### Data integrity and management

Data will be stored electronically on a database with secured and restricted access. Data transfer will be encrypted and any information capable of identifying individuals removed.

### Withdrawal

A participant will be considered to have withdrawn from the trial when consent is revoked or if the participant cannot be contacted or located. If this occurs, no further assessments will be performed. Participants will not be withdrawn from the trial for protocol violations.

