### Exclusion criteria

Participants will be excluded if they:

1. have any other type of neurological injury affecting the target hand (e.g. brachial plexus or peripheral nerve injuries)

2. have had trauma or surgery to the target hand or upper limb within the last 12 months

3. have had amputation of any digits on the target hand

4. are not able to sit out of bed for at least two hours per day over three consecutive days

5. have extensive fixed contractures in the upper limb of the target hand preventing use of the instrumented exercise workstation

6. have severe spasticity in the target hand or upper limb preventing use of the instrumented exercise workstation

7. are unable to attend the 6 month and 12 month follow-up assessments

8. are likely to undergo hand surgery in the target hand in the next year

9. are likely to experience autonomic dysreflexia or hypotension in response to FES

10. have any contraindications to FES such as cardiac pacemaker, epilepsy, forearm fracture or pregnancy

11. have intracranial metal implants

12. have impaired vision or are unable to view a computer screen

13. have any other serious medical condition likely to influence cooperation and adherence to the protocol including malignancies and psychiatric, behavioural or drug-dependency problems

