### Outcome assessments

Measurements will occur at baseline, 8 weeks after the commencement of the intervention period (8 weeks), and then at 6 months and 12 months after randomisation (see Table 1). There is a 3-week period after randomisation when all participants receive usual care prior to the commencement of the 8-week intervention period. This is to allow time for the delivery of the FES garments for experimental participants (these are custom made in Canada). For this reason, the 8-week assessments are 8 weeks after commencement of the intervention period but 11 weeks after randomisation.

**Table 1 T1:** Timeline of participants' progression through the trial

week -3	week -1	week 0	weeks 0 - 3	weeks 4 - 12	week 13 ^†^	weeks 14 - 25	week 26^§^	weeks 27 - 51	week 52^§^
screening	baseline assessment by blinded assessor	concealed random allocation	usual care for all participants^€^	8-week intervention **Exp**: Instrumented exercise workstation, FES and usual care **Control**: usual care	8-week assessment by blinded assessor	usual care for all participants	6-month assessment by blinded assessor	usual care for all participants	12-month assessment by blinded assessor

^† ^plus or minus 1-week window for commencement; 1-week window for completion upon commencement

^§ ^plus or minus 1-week window for commencement; 1-week window for completion upon commencement

^€ ^this 3-week period is to allow time for the ordering and delivery of the personalised FES garment for experimental participants

All assessments will be made by research therapists blinded to group allocation. Any inadvertent unblinding of assessors will be reported. In addition, the success of blinding will be estimated by asking assessors to guess participants' group allocations at the completion of each post-randomisation assessment.

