#### Analysis

The primary analysis of ARAT score at 8 weeks will be performed using an ANCOVA model that includes treatment group and site as factors, and the baseline ARAT score as a covariate. All secondary outcomes (including the ARAT at 6 months and 12 months) will be analysed using a mixed model repeated-measures (MMRM) approach where applicable (i.e. where data are collected at 8 weeks, 6 months and 12 months). Multiple imputation analysis will be performed to account for the effect of missing data.

Analyses will be performed by a blinded and independent statistician according to the intention-to-treat principle and using the full dataset comprising all randomised participants. In addition, the primary analysis on the 8 weeks ARAT data will be repeated using a per protocol dataset. This dataset will only comprise participants who adhered to all aspects of the protocol and received at least 80% of training sessions (i.e., control participants who received at least 80% of the 15-minute sessions of one-to-one hand therapy and experimental participants who received this as well as 80% of the training sessions with the instrumented exercise workstation and FES). All analyses will be performed using Stata (Version 11 or higher).

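### Loss of contact ends assessment for good, as revoked consent does, so a participant missed at 6 months and found again would not be assessed at 12 months

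*Protocol article*

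**What the plan says.** The Withdrawal section defines withdrawal by either of two events: "A participant will be considered to have withdrawn from the trial when consent is revoked or if the participant cannot be contacted or located". The next sentence gives the consequence, without distinguishing between them: "If this occurs, no further assessments will be performed". The section closes by keeping non-adherent participants in follow-up: "Participants will not be withdrawn from the trial for protocol violations".

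The Analysis section sets the analysis "according to the intention-to-treat principle and using the full dataset comprising all randomised participants". For the later visits it says: "All secondary outcomes (including the ARAT at 6 months and 12 months) will be analysed using a mixed model repeated-measures (MMRM) approach where applicable". For gaps it adds: "Multiple imputation analysis will be performed to account for the effect of missing data".

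Table 1, under Outcome assessments, places the 6-month visit at week 26 and the 12-month visit at week 52. Each has the window "plus or minus 1-week window for commencement; 1-week window for completion upon commencement". The exclusion criteria remove at entry those who "are unable to attend the 6 month and 12 month follow-up assessments".

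**The concern.** The two events differ in kind. A participant who revokes consent has decided that assessment should stop. A participant who cannot be reached has decided nothing: consent stands, and the state may last weeks rather than for good. The text gives both the same permanent consequence.

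At stake are 12-month observations that the trial would be entitled to collect and could use. The repeated-measures model can take a 12-month value from someone with no 6-month value, and the economic evaluation needs resource use over the 12-month follow-up. Where the rule prevents an assessment that could have been made, the plan relies on modelling and imputation in place of an observed value.

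The rule also fits poorly with the decision, in the same section, to keep protocol violators in follow-up. That decision shows an intention to follow as many people as possible.

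**Working it through.** This is mainly a comparison of sections, with a little arithmetic on timing and size.

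**1. When the stopping sentence has any effect.** There are three cases.
- Consent revoked: assessment must stop, so the sentence is needed.
- Contact lost and never regained: no assessment is possible, so the sentence changes nothing.
- Contact lost and later regained, consent still in force: an assessment is possible, and the sentence rules it out.

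For the loss-of-contact group, the sentence matters only in the third case.

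**2. Whether the third case can occur.** Inputs are the visit weeks and windows in Table 1.
- Latest end of the 6-month visit: 26 + 1 (late start) + 1 (completion) = week 28.
- Earliest start of the 12-month visit: 52 − 1 = week 51.
- Gap: 51 − 28 = 23 weeks at the least.

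The Follow-up period section expects care to pass to outside providers after discharge. A gap of 23 weeks or more leaves ample time for a lost participant to be found again.

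**3. Which data are exposed.** Nine secondary outcomes are measured at 12 months: ARAT, summed upper limb strength, AIS sensory, AsTex, AuSpinal, CUE, AQoL-8, HUI3 and SCIM self-care. Community resource use for the economic evaluation is collected over the same period. Goal attainment and perceived treatment effectiveness are measured at 8 weeks only.

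**4. The primary outcome.** This is the 8-week ARAT. The inclusion criteria expect a 12-week stay in the unit. The 8-week assessment falls 11 weeks after randomisation by the text under Outcome assessments, and at week 13 in Table 1. On either timing most participants should still be in, or only just out of, the unit, so loss of contact before the primary assessment is improbable.

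**5. The analysis set.** The Withdrawal section stops future assessments. It does not remove anyone from analysis or delete earlier data. The Analysis section keeps everyone randomised. The two sections are compatible.

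**6. Size.** The only loss rate in the article is the 10% allowance under Sample Size, and reproducing that calculation shows what it refers to.
- Adjusted SD: 14 × √(1 − 0.8²) = 8.4.
- Per group: 2 × (8.4 × (1.960 + 0.842) / 5.7)² = 34.09, rounded up to 35.
- With 10% drop-out: 35 / 0.9 = 38.9, rounded up to 39, so 78 in total.

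The stated 78 is reproduced. Every input concerns the 8-week ARAT, so the 10% is not a forecast of 12-month loss, and it says nothing about how many lost participants return.

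Let m be the number lost around week 26 and found by week 52. Their 6-month visit is missing under any rule, so the rule itself costs m 12-month visits, or m/78 of those planned. With m = 0 the cost is nil. Each person adds 1/78 = 1.3%. The article gives no value for m.

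**The case against.** The strongest reply is that the wording describes ordinary loss to follow-up: a person who cannot be reached cannot be assessed, so nothing obtainable is given up. The article is also a condensed account. The number of contact attempts and the procedure for renewed contact would normally stand in the full protocol, and their absence here is no fault. Entry criteria already screen out people who could not attend the later visits.

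Much of this stands. A reader might infer that one failed contact is enough to close follow-up, but the text says nothing of the kind and gives no number of attempts. A reader might also infer a contradiction with intention to treat. There is none, because a withdrawn participant remains in the analysis set and earlier data are kept. Nor does the article show that people who lose contact differ in function or care burden. That is plausible, but an argument that the rule strains the missing-at-random assumption would be conjecture.

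What does not stand is the claim that the rule costs nothing. That is true only while contact remains lost. The stopping sentence is stated rather than omitted, it covers both events, and it makes no exception for someone who is found again.

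**Conclusion.** The point holds in a narrow form. As written, a participant who still consents, is lost around 6 months and is found by 12 months would not be assessed at 12 months. The consequence is avoidable missing data in secondary and economic outcomes. The intention-to-treat set is unaffected and the 8-week primary result hardly so.

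The size is unknown and may be near zero. A reader might take 10% of 78 = 7.8 participants, suppose that a quarter to a half are only temporarily out of contact, and arrive at about 2 to 4. The documents do not support this: the 10% belongs to the 8-week sample size, and the fraction has no source.

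The conclusion rests on reading the two Withdrawal sentences literally and on the article reflecting the full protocol. If the full protocol already provides for renewed contact, only the article's wording is at issue. The change is worth making because it is cheap, not because a large loss has been shown.

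**What to change.** Reword the Withdrawal section so that:
- withdrawal means revoked consent only;
- failure to reach a participant at a scheduled visit counts as a missed visit;
- each later scheduled assessment is attempted in everyone who has not revoked consent.

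The analysis set, the repeated-measures model and the use of multiple imputation can stay as they are. The cost is a sentence or two of protocol text and a few extra contact attempts. There are no new visits or measurements, and the sample size does not change.

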### Monitoring

The trial will be overseen and monitored by a program manager. The program manager will visit each site to examine trial procedures, ensure data quality and monitor compliance with the trial protocol. Three safety variables will be monitored and documented throughout the trial. These are self-reported pain (using an 11-point category rating scale), blood pressure and skin irritation from the stimulating electrodes. However, only two safety variables (pain and blood pressure) are considered serious enough to warrant inclusion in the safety interim analysis. This analysis will be undertaken when 40 patients have completed the 8-week assessment. It will be done by an Independent Data Safety Monitoring Board comprising a statistician and two rehabilitation doctors. If there are concerns about the safety of participants, this board will make a recommendation to the trial steering committee about continuing, stopping, or modifying the trial. The Haybittle-Peto procedure for generating early stopping boundaries will be used. A recommendation of early termination due to experimental treatment inferiority on pain (mean margin of 4/10) or blood pressure (mean margin of 40 mmHg) will be considered by the Independent Data Safety Monitoring Board if the corresponding Haybittle-Peto boundary (p = 0.003, Z = 3) at a given interim analysis is crossed. No formal interim analyses for efficacy or futility are planned.

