### Randomisation

Participants will be randomly assigned to either control or experimental group with a 1:1 allocation as per a computer generated randomisation schedule stratified by site and the baseline score of the Action Arm Research Test (ARAT; <= 21 versus >21) using permuted blocks of random sizes. The block sizes will not be disclosed, to ensure concealment.

Prior to commencement of the trial, an independent researcher with no clinical involvement in the trial will use a computer random number generator to produce the randomisation schedule. Randomisation will occur after completion of baseline assessments by contacting an administrator independent of the recruitment process and located off site at Neuroscience Trials Australia, for allocation assignment. A participant will be considered to have entered the trial once his/her randomisation is revealed.

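### The only numerical safety trigger compares arm means against margins whose role in the test is undefined, and under any reading it is nearly blind to severe events in a few participants

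*Protocol article*

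**What the plan says.** All of the rule stands in the Monitoring section of the protocol article.

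- **Variables recorded throughout the trial:** "self-reported pain (using an 11-point category rating scale), blood pressure and skin irritation from the stimulating electrodes". Of these, "only two safety variables (pain and blood pressure) are considered serious enough to warrant inclusion in the safety interim analysis".
- **Timing:** "This analysis will be undertaken when 40 patients have completed the 8-week assessment". Under Randomisation, participants are "randomly assigned to either control or experimental group with a 1:1 allocation", which gives about 20 per arm at that point.
- **Trigger:** early termination for experimental-treatment "inferiority on pain (mean margin of 4/10) or blood pressure (mean margin of 40 mmHg) will be considered" by the independent board if the corresponding "Haybittle-Peto boundary (p = 0.003, Z = 3) at a given interim analysis is crossed".
- **Other looks:** "No formal interim analyses for efficacy or futility are planned".
- **Board's remit:** if the board has concerns about participants' safety, it advises the steering committee on whether the trial should go on, stop or change. This remit is not tied to the boundary.

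The section gives no standard deviation for pain or blood pressure. It does not say which blood pressure measure is compared or in which direction. Exclusion criterion 9 keeps out people who "are likely to experience autonomic dysreflexia or hypotension in response to FES", so the protocol itself identifies these two reactions as risks of the stimulation.

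**The concern.** There are two separate problems.

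First, the rule names a margin and a critical Z but not the hypothesis that joins them. The wording about inferiority with a margin suggests that the margin is the null value, but two other readings are possible. They give very different chances of firing for the same true difference, so the board would not know what a crossed or an uncrossed boundary means.

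Second, the statistic fits poorly with the harm that the protocol foresees. Dysreflexia and hypotension happen to individuals and move pressure in opposite directions. A difference in arm means spreads a few severe events over the whole arm and, if the measure is signed, lets rises and falls offset each other.

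What is at stake is how the interim review is read. An uncrossed boundary could be taken as reassurance when several participants have had severe reactions.

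**Working it through.** **Inputs.** From the protocol article: 40 completers, 1:1 allocation, margins of 4 points and 40 mmHg, Z = 3, stated p = 0.003. Assumed, because the document gives none: SD of 2 to 3 for pain and 15 to 25 mmHg for blood pressure, with 30 mmHg as a wider case.

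**The stated boundary reproduces.** Two-sided p at Z = 3 is 2 × (1 − Φ(3)) = 0.0027, which rounds to 0.003. The one-sided value is 0.00135.

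**Standard error.** SE = SD × √(2/20) = SD × 0.316.
- Pain, SD 2 / 2.5 / 3: SE 0.63 / 0.79 / 0.95.
- Blood pressure, SD 15 / 20 / 25 / 30: SE 4.74 / 6.32 / 7.91 / 9.49 mmHg.

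**Reading 1: the margin is the null value.** The observed mean difference must reach margin + 3 × SE.
- Pain: 4 + 3 × 0.63 = 5.9; 4 + 3 × 0.79 = 6.4; 4 + 3 × 0.95 = 6.8 points.
- Blood pressure: 40 + 3 × 4.74 = 54; 40 + 3 × 6.32 = 59; 40 + 3 × 7.91 = 64 mmHg.
- If the true difference equals the margin, the rule fires with probability 1 − Φ(3) = 0.13% at any SD. This follows by construction, as that is the null.

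**Reading 2: the observed difference must exceed the margin and Z against zero must exceed 3.** Here 3 × SE is below the margin in every case above (at most 2.85 points or 28.5 mmHg), so the margin decides. A true difference equal to the margin is flagged 50% of the time. A true excess of 3 points (SD 2.5) is flagged with probability Φ((3 − 4)/0.79) = 10%, and one of 30 mmHg (SD 20) with probability Φ((30 − 40)/6.32) = 6%.

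**Reading 3: the null is zero and the margin is the effect to detect.** The chance of firing is Φ(margin/SE − 3).
- Pain, SD 2 / 2.5 / 3: 99.96% / 98% / 89%.
- Blood pressure, SD 20 / 25 / 30: 99.96% / 98% / 89%.
- A t test at the same p lowers the 89% to 83%.

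**Harm in a few participants, 20 per arm.**
- Five of 20 experimental participants rise by 60 mmHg: mean shift 5 × 60/20 = 15 mmHg. The same events widen the spread. With SD 15 their added variance is 60² × 0.25 × 0.75 = 675, so the experimental arm's variance is 225 + 675 = 900. SE is then √(900/20 + 225/20) = 7.5, and the expected Z is 15/7.5 = 2, short of 3.
- Simulating this case (40,000 trials for each SD from 10 to 25), the rule fires in 4 to 7% under reading 3 and in under 0.1% under readings 1 and 2.
- Five rises and five equal falls: shift (5 × 60 − 5 × 60)/20 = 0. With half the arm affected, the rule fires in about 0% under every reading.
- Four of 20 with 6 more pain points: shift 4 × 6/20 = 1.2 points. With SD 2 to 3 the rule fires in 2 to 3% under reading 3 and in under 0.2% otherwise.

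**The case against.** A reader might infer that the rule cannot detect harm at all because 20 per arm at Z = 3 is too few and too strict. The document does not support that. Under reading 3, a uniform shift as large as the margin is caught about 89% of the time or more across the assumed SDs. The weakness lies in the undefined role of the margins and in the use of means, not mainly in the sample size or the critical value.

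Nor is the boundary the only route to stopping. The variables are monitored throughout, the board can act on any safety concern, and crossing the boundary only leads the board to consider a recommendation. The rule is already advisory, so asking for it to be made non-binding would change nothing.

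It is also tempting to say that Z = 3 should be dropped because no efficacy look is planned and no alpha needs protecting. That goes too far: a strict boundary also limits false alarms, so removing it is a trade-off.

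Two further points carry some weight. The protocol does not say that the boundary targets dysreflexia or hypotension; that link is inferred from an exclusion criterion, which removes the people at highest apparent risk. The cancelling of rises and falls assumes a signed measure. A condensed article may also leave the measure's definition and the review of individual events to a full protocol or board charter. None of this answers the dilution of individual events, which holds under all three readings of the rule as stated.

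**Conclusion.** The point holds as a should-fix. The article fixes a numerical safety trigger whose chance of firing at a true difference equal to its own margin is 0.13%, 50%, or about 89% or more, depending on a reading that it does not specify. Under the reading closest to its wording, the observed mean difference would have to reach about 5.9 to 6.8 pain points or 54 to 64 mmHg. Under every reading, severe events in a quarter of the experimental arm would usually leave the boundary uncrossed.

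The figures rest on about 20 per arm, a normal approximation and the assumed SDs. The 0.13% does not depend on the SD; the 50% holds wherever 3 × SE is below the margin, as it is throughout the range used. The size of the individual events is illustrative. The primary analysis is not affected, and the other safeguards stay in place, which is why this is not rated higher.

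**What to change.** In the Monitoring section and the board's charter:

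1. For the interim safety review, tabulate by arm each participant's worst pain increase, largest pressure rise and largest pressure fall, keeping rises and falls separate. Give the number and proportion beyond limits set by the board, with exact confidence intervals. The clinical limits are for the board to choose.
2. For any mean comparison that is kept, state the null hypothesis, the role of the margin, the blood pressure measure and the direction.
3. State that an uncrossed mean boundary is not evidence of safety.

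This uses safety data already recorded and needs no extra participants. It costs no alpha for the primary analysis. The price is some rewording, a little more tabulation and a somewhat higher chance of an unnecessary board discussion.

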## Discussion

This trial will provide information about the effectiveness of an intensive task-specific hand training program provided with FES through an instrumented exercise workstation. Hand function in people with tetraplegia is central to their quality of life. Any treatment that can improve their hand function has the potential to make real and important differences to the lives of those affected by SCI.

This trial will adhere to key methodological principles important for minimising bias and will be reported according to the CONSORT guidelines. For example, allocation will be concealed and randomised, assessors will be blinded and analyses will be performed on an intention-to-treat basis. Therapists and participants will not be blinded due to the nature of the intervention.

One primary outcome and a number of secondary outcomes will be used. The primary outcome reflects unilateral hand function. The secondary outcomes include measures of impairment, activity limitation and participation restriction, and encompass both objective measures as well as participants' perceptions.

It is anticipated that this trial will take three years to complete. Recruitment commenced in December 2009 with the first participant randomised in February 2010. Recruitment will continue until mid 2011. The one-year follow up assessments will be completed in 2012.

